### Masking, randomization, and data safety monitoring

Based on feedback from family and provider stakeholders gathered during the development of this proposal, participants will not be masked. Randomization will occur at the individual level using a random number generator in blocks of two to ensure that participants within the settings are allocated equally to conditions. Randomization will be conducted by an independent party and study coordinators will be unaware of the randomization allocation until participant enrollment. Allocation will be revealed via a blinded excel file after participant enrollment. This study adheres to the SPIRIT guidelines.

We have developed an ethically approved data safety and monitoring plan. This plan involves obtaining informed and written consent from the guardian(s) as well as assent from all participants, by the designated research coordinator, and safely storing data and restricting unauthorized access to identifiable participant information. Additionally, this plan outlines the protocol for responding to any adverse events/reactions to the randomly assigned treatment options. While this study is low-risk, there is a limited possibility that participants in this study will experience unknown effects. Therefore, the study team will closely monitor the acceptability of the procedures and seek to understand any concerns from participants and guardian(s) to ensure they are addressed in a timely matter. If a formal concern is voiced by a participant or by their guardian(s), which is possible at any time (via provided study contact information), it will be immediately addressed to the best of the study team’s ability and will also be reported to the ethics board. Discontinuation of the study protocol will be made at the participants’, ethics board, and/or monitoring boards’ request. No specific modifications are considered at the present time.

A Data Safety and Monitoring Board (DSMB) will monitor all clinical outcomes and adverse events. This includes hospitalization(s), changes in mental health presentation, and contact with the START crisis response team. Since START is a crisis prevention and intervention program, it is designed to handle clinical events through prespecified protocols and a robust clinical team. The DSMB will be led by an independent team made of three psychologists, and a family advocate. No members of the DSMB team have direct involvement with the study or any conflict of interest (COI) with the investigators conducting the study. No interim analyses or stopping rules have been defined by the DSMB, as of yet.

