**Methods:**

This study will take place within START (Systemic, Therapeutic, Assessment, Resources, and Treatment), a national evidence-based model of mental health crisis prevention and intervention for people with IDD. A total of 500 youth and adults, located across nine states, will be randomized 1:1 to telemental health vs. in-person. Participant inclusion criteria are ages 12–45 years, living in a family setting, and newly enrolled (within 90 days) to START. Outcomes will be assessed, using a non-inferiority design, for up to 1 year or until discharge. The intervention is comprised of four components: (1) outreach; (2) consultation/coping skills; (3) intake/assessment; and, (4) 24-hour crisis response. The in-person condition will deliver all components in-person. The telemental health condition will deliver components 1 & 2, via telephonic or other communication technology, and components 3 & 4 in-person. Outcomes include mental health crisis contacts, mental health symptoms, emergency psychiatric service use, perceived quality of mental healthcare, and time to discharge.

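### Fixed blocks of two in an unmasked trial let anyone who tracks allocations at a setting deduce the second arm of each pair before enrollment

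*Protocol article*

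**What the plan says.** All quotes but one are from the protocol article, section Masking, randomization, and data safety monitoring.

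- Method and stated purpose of the blocks: individuals are randomized "using a random number generator in blocks of two to ensure that participants within the settings are allocated equally to conditions".
- Ratio (abstract, Methods): participants "will be randomized 1:1 to telemental health vs. in-person", so each block of two holds one of each arm.
- Masking: "participants will not be masked".
- Safeguards: "Randomization will be conducted by an independent party and study coordinators will be unaware of the randomization allocation until participant enrollment", and "Allocation will be revealed via a blinded excel file after participant enrollment".

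The article does not say that block size varies or is kept from recruiting staff. It implies separate lists per setting but does not name site as a stratification factor.

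**The concern.** In a 1:1 block of two, the second allocation is always the opposite of the first. Remote and home-based delivery are easy to tell apart, so a local team knows each arm once it is revealed. The two safeguards hide the list, but the next arm can be worked out without opening it. The assurance that "study coordinators will be unaware of the randomization allocation until participant enrollment" therefore cannot be guaranteed for second members of pairs.

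The article leaves room for this knowledge to be used. Eligibility runs for up to 90 days after START entry (Setting and inclusion criteria), so the timing of enrollment is flexible. Staff may also hold views on who suits which mode. The Comparators section keeps two components in person for rapport and safety, and the Study aims section expects better perceived quality with telemental health in rural settings.

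At stake is the comparability of the arms. If lower-risk people were steered to telemental health, the comparison could move towards non-inferiority. This is clearest for crisis contacts, which depend directly on risk. Neither the intention-to-treat nor the per-protocol analysis repairs a selected allocation.

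**Working it through.** The article gives no predictability figure to reproduce, so the check starts from the block size.

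**Inputs.** Block size 2, ratio 1:1, N = 500. Table 1 gives 8 + 1 + 1 + 3 + 5 + 3 + 1 + 5 + 1 = 28 sites, so 500 / 28 ≈ 18 participants per site. The Non-inferiority design section equates 7 FEIS points with a standardized 0.5, so the SD is 7 / 0.5 = 14 points.

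**1. Predictability with blocks of two, one list per site.** The first of a pair is a coin toss and the second is certain.
- Share certain: 1/2 = 50%.
- Best-guess accuracy: (0.5 + 1) / 2 = 75%, against 50% for unpredictable allocation.

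**2. Number of participants.**
- Near-equal sites (24 with 18 and 4 with 17): 24 × 9 + 4 × 8 = 248 second members.
- Every site ending mid-pair: (500 − 28) / 2 = 236.
- Every pair complete: 500 / 2 = 250.

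**3. Comparison with other block sizes.** For a 1:1 block of size 2m, the expected share of certain allocations is 1/(m + 1). Best-guess accuracy comes from enumerating all sequences. The hidden-size row is a simulation (18 participants per site, 4,000 runs) of an observer who knows which sizes are in use but not which was drawn.

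| Scheme | Certain | Best guess correct |
|---|---|---|
| Fixed 2 | 50% | 75% |
| Fixed 4 | 33% | 71% |
| Fixed 6 | 25% | 68% |
| Mixed 4/6, current size known | 28% | 69% |
| Mixed 4/6, current size hidden | about 6% | about 68% |

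The known-size row follows from the two fixed rows: (4 × 1/3 + 6 × 1/4) / 10 = 28%, and (4 × 0.708 + 6 × 0.683) / 10 = 69%.

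**4. Illustration of bias.** Two inputs are assumptions with no source in the article: staff act on 25% of predictable slots, and the participants affected differ by 0.5 SD.
- Share of an arm affected: 0.5 × 0.25 = 0.125.
- Steering in one arm only: 0.125 × 0.5 SD = 0.0625 SD; × 14 = 0.875 FEIS points, or 12.5% of the margin.
- Opposite steering in both arms: 2 × 0.0625 = 0.125 SD; × 14 = 1.75 points, or 25% of the margin.

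**5. If one central list is used instead.** A site sees only its own part of a sequence spread over 28 sites, so it could rarely deduce the next arm. But a pair could then be split between two sites, and blocks of two would not secure the within-setting balance given as their purpose.

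**The case against.** Several points on the other side stand.

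- **Per-setting lists are inferred.** The purpose clause makes this the likelier reading, but the 50% figure depends on it.
- **Concealment is not lost outright.** A reader might infer that it is defeated, or that the assurance about coordinators is untrue for half the sample. The article does not support that. An independent party runs the randomization, first members stay concealed, and deduction requires someone to know the block size and follow the sequence. Consent is taken by a designated research coordinator, who is not shown to be the START coordinator delivering care. Nothing shows that families would know the previous allocation.
- **Harm is not certain, nor is its direction.** A reader might infer a false non-inferiority result that no analysis could remove. Outcomes are analyzed as changes from baseline, and high-need participants may have more room to improve, which could favor the in-person arm. The article does not link severity to FEIS change. Baseline symptoms and FEIS are measured, so imbalance on them can be detected and adjusted for. The planned adjustment names sociodemographic differences only, and unmeasured judgment about suitability would remain.
- **The fix is partial.** If a recruiter steered on every best guess between types differing by D, the bias would be D × (2p − 1), where p is best-guess accuracy. That is 0.50D at p = 0.75 and 0.36D to 0.38D at p = 0.68 to 0.69. The main gain is in allocations known for certain.

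What does not stand is the idea that the existing safeguards are enough. They control access to the list, while the weakness lies in the sequence itself.

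**Conclusion.** The point holds as a design weakness. With blocks of two within settings and visible treatment, up to 50% of allocations (about 236 to 250 of 500) can be deduced before enrollment by someone who knows the block size and has seen the first of the pair. Best-guess accuracy is 75%. This rests on lists being run per setting. On a central list predictability at a site is low, but the stated purpose of the blocks is then not met, so the sentence needs correction on either reading.

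The consequence is a risk of selective enrollment that could favor non-inferiority, most clearly for crisis contacts. The range of about 0.06 to 0.125 SD (0.9 to 1.75 FEIS points) shows scale under assumed behavior and is not an estimate of actual bias. Baseline adjustment would correct only measured differences.

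**What to change.** Replace the blocks of two with computer-generated permuted blocks of randomly varying size (for example 4 and 6), explicitly stratified by site, with sizes withheld from recruiting staff. Keep the release of each allocation one at a time after enrollment, and state that it follows completed consent and baseline assessment. The article expected its first enrollment in Spring 2023, so keep any allocation already made and apply the new list from the next participant.

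The cost is a regenerated list and a rewritten sentence. Temporary within-site imbalance can reach 3 instead of 1, which is small with about 18 participants per site; a site switched mid-pair also carries over an imbalance of 1. Certain allocations fall from 50% to about 6% with sizes hidden (28% if the current size is known), and best-guess accuracy from 75% to about 68–69%.

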### Non-inferiority design

This study will employ a non-inferiority design. Non-inferiority trials permit a ‘new’ treatment to be considered efficacious if treatment effects fall within a pre-specified margin (the non-inferiority [NI] margin) of the effects identified in the reference treatment [27]. In this study, the ‘new treatment’ will be the telemental health condition, while the in-person condition will serve as the ‘established/reference treatment’. The merits of telemental health that justify consideration as an alternative to the standard of care include increased accessibility and lower cost. The merits of telemental health are assumed to be valuable enough that, even if effects fall slightly short of the reference treatment by a clinically tolerable amount, it is a viable alternative to the standard of care when circumstances would indicate its use [28].

The NI margin has been set for the FEIS, given its primacy in outcome. A 7-point change in the total FEIS score, which is equivalent to a standardized delta of 0.5, will identify the lower threshold for clinically meaningful difference [21]. Thus, a 99% confidence interval for the slope for the group assignment variable will be constructed and its lower limit will be compared to the − 7.0 non-inferiority margin. The 99% confidence interval, reflecting the α cutoff of 0.008, was selected to account for multiple comparisons, which will be determined post-hoc via the Benjamini Hotchberg procedure [29]. The non-inferiority margin for emergency service use will be a 38% reduction in the probability of a START crisis contact between START in-person and START telemental health. Last, we have identified a five-point change in the ABC irritability subscale as the non-inferiority margin. This study was registered on April 20th, 2022 on clinicaltrials.gov (NCT05336955; https://clinicaltrials.gov/ct2/show/NCT05336955 ).

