### Statistical analyses

The efficacy analyses will be conducted as both intention-to- treat (ITT; “as allocated”) and per protocol (PP; “as-treated”) since ITT can bias towards the null, leading to false claims of non-inferiority, and PP can fail to preserve the balance inherent to randomization (30, 31). For the analysis, the first step will be to examine demographic and clinical characteristics across study conditions to assess that the randomization worked as expected. If significant sociodemographic differences emerge, these variables will be included in the multivariate analyses since baseline adjustment has been shown to increase precision in randomized control trials (32). All analyses, for the factorial design, will be examined using a series of multilevel (or “mixed” effects) general linear regression models that account for clustering (via a random intercept) across sites. For these models, the independent variable of interest will be telemental health versus in-person START. The dependent variables will be calculated as change scores/differences since baseline. Two-way (Intervention group x time) interaction terms will test the primary study aim. Three-way (Intervention group x demographic population x time) interaction terms will test the secondary study aim. Effect sizes will be calculated using Cohen’s *d*. To accommodate increased false discovery rate, the study will adjust the significance threshold using the Benjamini-Hochberg procedure. This procedure is conducted after all tests are concluded; α = .01 will be assumed for the power analysis.

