### Power analyses

Using data from Kalb et al. 2019 [21], we calculated the sample sizes needed to have 80% statistical power to detect the above-mentioned non-inferiority margins with α set at 0.008. For changes in total FEIS scores from baseline to follow-up between the study arms, this study requires N = 128 per group. For a 38% reduction in the probability of a START crisis contact between conditions, this study requires N = 250 per condition. For changes in the mean Aberrant Behavior Checklist irritability scores, this study requires N = 100 per condition.

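### Two incompatible significance levels (0.01 and 0.008, sidedness unstated) govern the non-inferiority decisions, and the fixed 99% interval is not reconciled with the Benjamini-Hochberg step

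*Protocol article*

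**What the plan says.** All of this is in the protocol article.

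- **Non-inferiority design**, on the FEIS decision: "a 99% confidence interval for the slope for the group assignment variable will be constructed and its lower limit will be compared" with a margin of -7.0 points, described as a standardized difference of 0.5.
- **Non-inferiority design**, on the level of that interval: "The 99% confidence interval, reflecting the α cutoff of 0.008, was selected to account for multiple comparisons, which will be determined post-hoc", with Benjamini-Hochberg named as the procedure.
- **Statistical analyses**, after naming Benjamini-Hochberg again: "This procedure is conducted after all tests are concluded; α = .01 will be assumed for the power analysis".
- **Power analyses**, on the same sample-size work: "80% statistical power to detect the above-mentioned non-inferiority margins with α set at 0.008".
- **Power analyses**, on the FEIS: "For changes in total FEIS scores from baseline to follow-up between the study arms, this study requires N = 128 per group".

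No section says whether any alpha is one- or two-sided. None gives the false-discovery level q or the number of tests in the Benjamini-Hochberg family.

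**The concern.** A non-inferiority verdict is a comparison of one confidence limit with one margin, so the level of that limit is the decision rule. Here the level appears as 99%, as 0.008 and as 0.01, and the text equates the first two although they differ. Two sections then disagree on the alpha behind one power analysis.

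The second difficulty is that two rules are named for the same decision. A fixed 99% interval has a cutoff known in advance. A Benjamini-Hochberg cutoff depends on the p-values of the other tests and is known only once all of them are in. An FEIS result could pass under one and fail under the other, and the article does not say which prevails or how they combine. This bears on a confirmatory claim for an outcome to which the article gives primacy when setting the margin.

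The FEIS sample size is a lesser matter: it should follow from the printed margin, power and alpha, and it does not.

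**Working it through.** **1. What level does each statement imply?**

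| Statement | Two-sided level | Error on the limit tested | z |
|---|---|---|---|
| 99% interval, or 0.01 two-sided | 0.01 | 0.005 | 2.576 |
| 0.008 two-sided (99.2% interval) | 0.008 | 0.004 | 2.652 |
| 0.008 one-sided (98.4% interval) | 0.016 | 0.008 | 2.409 |

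The 99% interval and 0.01 agree if 0.01 is two-sided. On neither reading does 0.008 give a 99% interval. The article therefore holds two levels.

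**2. Does the stated FEIS sample size reproduce?**

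Inputs: margin 7 points = 0.5 SD (Non-inferiority design), so SD = 7/0.5 = 14; 80% power (Power analyses); 1:1 allocation (Abstract); true difference taken as 0.

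Formula: n per group = 2(z + 0.842)²/0.5².

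| Alpha | Calculation | n, normal | n, t-based |
|---|---|---|---|
| 0.008 two-sided | 2(2.652 + 0.842)²/0.25 = 97.6 | 98 | 100 |
| 0.01 two-sided (99% interval) | 2(2.576 + 0.842)²/0.25 = 93.4 | 94 | 96 |
| 0.008 one-sided | 2(2.409 + 0.842)²/0.25 = 84.5 | 85 | 86 |
| 0.01 one-sided | 2(2.326 + 0.842)²/0.25 = 80.3 | 81 | 82 |

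The stated 128 is not among these. With 128 per group, power at 0.5 SD is about 91% (0.008 two-sided), 92% (0.01 two-sided), 94% (0.008 one-sided) or 95% (0.01 one-sided), against the stated 80%.

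Inputs that the article does not print could produce it: 25% attrition (96/0.75 = 128), a design effect of about 1.3 (128/98 = 1.31), or a change-score SD of about 16 at 0.008 two-sided (14 × √(128/98) = 16.0).

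**3. How far does the FEIS verdict move between rules?**

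Assumptions: all 250 per arm analysed, SD 14, no clustering or attrition. SE = 14 × √(2/250) = 1.252. The worst observed difference that still passes is -7 + z × SE.

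| Rule | z | Worst passing difference |
|---|---|---|
| 99.2% interval | 2.652 | -3.68 |
| 99% interval | 2.576 | -3.77 |
| 98.4% interval | 2.409 | -3.98 |
| Benjamini-Hochberg, q = 0.05 assumed, last rank, two-sided | 1.960 | -4.55 |
| Same, one-sided | 1.645 | -4.94 |
| Benjamini-Hochberg, q = 0.01 assumed, last rank, two-sided | 2.576 | -3.77 |
| Same, one-sided | 2.326 | -4.09 |

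For m tests, the Benjamini-Hochberg cutoff at rank k is kq/m, so the last rank (k = m) is the loosest and equals q; earlier ranks are stricter. Against the 99% interval, the gap at q = 0.05 is 4.55 - 3.77 = 0.78 to 4.94 - 3.77 = 1.17 points on a 7-point margin. Among the three interval levels it is at most 3.98 - 3.68 = 0.30 points. If only 128 per arm were analysed, SE = 14 × √(2/128) = 1.75 and every gap would be 1.75/1.252 = 1.4 times as large.

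**The case against.** The strongest reply is that this is mostly rounding. On two decimals 0.008 becomes 0.01, and 99.2% becomes 99%. If so, the FEIS limit moves only from -3.68 to -3.77 and the sample size from 100 to 96. That is plausible, but the article does not say it, and Power analyses and Non-inferiority design print 0.008 as the working value. The small size of this gap stands; the contradiction remains.

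A reader might infer that investigators are free to choose the threshold once results are in. The text does not support that. Benjamini-Hochberg is named in advance in two sections, and computing its cutoffs from the observed p-values is how the procedure works. What stands is narrower: its q and family are not given, and nothing says how it combines with a fixed 99% interval. The larger shifts to -4.55 or -4.94 depend on an assumed q of 0.05.

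A reader might also infer that 128 is a total mislabelled as per group, because 0.5 SD at two-sided 0.05 and 80% power needs 64 per group, 128 in all. The match is suggestive only. The calculation used data from a cited earlier study, and a condensed article may omit an attrition, clustering or SD allowance. Nor can the ABC figure of 100 per condition be tied to the FEIS calculation, since no ABC SD is given.

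**Conclusion.** The point holds as an internal contradiction in the decision rule. The article gives two levels, 0.01 and 0.008, without sidedness; it equates a 99% interval with 0.008, which is wrong on either reading; and it gives both levels for one power analysis. It would be too much to say that there are three levels, since the 99% interval and 0.01 coincide when two-sided.

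The fixed interval and Benjamini-Hochberg are unreconciled and can give different FEIS verdicts. Under the assumptions of 250 analysed per arm, SD 14 and independent observations, the practical difference is small among the interval levels. Between the 99% interval and Benjamini-Hochberg it runs from nothing (q = 0.01, two-sided) to about 1.2 points (q = 0.05, one-sided). Because this threshold decides the non-inferiority claim, it should be made unique before results are seen.

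The FEIS figure of 128 per group is not reproducible from the printed inputs, but is not shown to be wrong. It does not mean that the FEIS comparison is underpowered: 128 exceeds the 82 to 100 per group that the inputs require, and the trial plans 500 participants, 250 per arm.

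**What to change.** - State one alpha and its sidedness, use the matching interval for the margin-based outcomes, and make Non-inferiority design, Statistical analyses and Power analyses agree. One coherent choice is 0.008 two-sided with a 99.2% interval; the 0.01 in Statistical analyses would then become 0.008. The article does not itself say that 0.008 is two-sided, so this is a decision for the sponsor to make and record.
- Settle the role of Benjamini-Hochberg. Either base the non-inferiority decisions on the fixed interval alone and keep the procedure for the other tests, or fix its q and test family now and state how it sets the interval level for each non-inferiority decision.
- Restate the FEIS requirement, or give the SD, attrition or design effect that leads to 128 per group.

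The cost is wording and at most one restated number. Under the 99.2% option the interval widens slightly (z 2.65 instead of 2.58), and the planned 250 per arm still exceeds the 100 per group needed for the FEIS.
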